## Abstract

**Background:**

The literature suggests that person-centred care can contribute to quality of life and wellbeing of nursing home residents, relatives and staff. However, there is sparse research evidence on how person-centred care can be operationalised and implemented in practice, and the extent to which it may promote wellbeing and satisfaction. Therefore, the U-Age nursing home study was initiated to deepen the understanding of how to integrate person-centred care into daily practice and to explore the effects and meanings of this.

**Methods:**

The study aims to evaluate effects and meanings of a person-centred and thriving-promoting intervention in nursing homes through a multi-centre, non-equivalent controlled group before-after trial design. Three nursing homes across three international sites have been allocated to a person-centred and thriving-promoting intervention group, and three nursing homes have been allocated to an inert control group. Staff at intervention sites will participate in a 12-month interactive educational programme that operationalises thriving-promoting and person-centred care three dimensions: 1) Doing a little extra, 2) Developing a caring environment, and 3) Assessing and meeting highly prioritised psychosocial needs. A pedagogical framework will guide the intervention. The primary study endpoints are; residents’ thriving, relatives’ satisfaction with care and staff job satisfaction. Secondary endpoints are; resident, relative and staff experiences of the caring environment, relatives’ experience of visiting their relative and the nursing home, as well as staff stress of conscience and perceived person-centredness of care. Data on study endpoints will be collected pre-intervention, post-intervention, and at a six-month follow up. Interviews will be conducted with relatives and staff to explore experiences and meanings of the intervention.

**Discussion:**

The study is expected to provide evidence that can inform further research, policy and practice development on if and how person-centred care may improve wellbeing, thriving and satisfaction for people who reside in, visit or work in nursing homes. The combination of quantitative and qualitative data will illuminate the operationalisation, effects and meaning of person-centred and thriving-promoting care.

**Trial registration:**

The trial was registered at ClinicalTrials.gov March 19, 2016, identifier NCT02714452.

## Background

Current demographic changes with rapidly ageing populations pose challenges for aged care in terms of innovative, cost-effective and evidence-based ways to support wellbeing and health in frail older people [1, 2]. Aged care has predominantly had a negative societal image in many countries [3], and residents in nursing homes face the risk of limited possibilities to engage in self-selected and valued activities, and to keep in touch with the community outside of the nursing home [4, 5]. This involves serious threats to experiences of health and thriving for residents, whilst relatives report barriers to interacting with and being involved in care in the nursing home to the extent they wish [6, 7]. In addition, a negative societal image of aged care has implications for nursing home staff job satisfaction, contributing to challenges with recruiting and retaining skilled care professionals [3]. Previous research has also shown that nursing home staff experience high levels of stress [8]. Ideally, nursing homes places where frail older people can be supported to thrive despite illness and frailty [9, 10], but in reality many nursing homes struggle to provide more than just the basic physical care. Is it more surviving than thriving?

Thriving is an emerging concept in long-term care, referring to a person’s subjective experience of wellbeing in relation to the place in which they live. From the perspective of frail older people, thriving has been described as experiences of a good life, despite ill health and dependence [11–13]. An increasingly recognised facilitator of thriving within institutional environments is a caring environment, which refers to a holistic experience of the interaction between the physical and psychosocial environment, people’s doing and being within the environment, and a shared philosophy of care [14]. Person-centred care has been described as a philosophy of care to promote independence, authority and choice, and shared decision making for nursing home residents and their relatives [15–17]. However, there is an ongoing discussion in the literature on how person-centred care can be operationalised and implemented in practice, and the extent to which this actually can promote thriving, wellbeing and satisfaction for nursing home residents, relatives and staff. As described by Brownie [18], the concept and philosophy of person-centred care has been well described, developed and refined through conceptual work, and a number of studies have explored a variety of interventions with different endpoints [18]. Some interventions have been related to specific care situations such as bathing, mouth care or morning care [19–21], and others have focused on developing the physical environment to meet the needs of people with dementia [22, 23]. A few intervention studies have had a multi-dimensional, holistic, and individually tailored approach [24, 25], or been part of the conceptual development of person-centred care for example through life story work [26, 27]. Yet, conclusive evidence for effects on resident wellbeing and satisfaction has not yet been clearly established [22, 24, 25, 28, 29]. In addition, even though there is some emerging evidence for positive effects on job satisfaction and work related stress from providing person-centred care among care staff [30, 31], and higher satisfaction with care among relatives [32], further exploration has been recommended [33].

To conclude, the literature indicates that interventions aiming to improve the situation of nursing home residents, relatives and staff would benefit from having a person-centred approach [33, 34], even if further evidence is needed [18]. No previous controlled trials have been located that have evaluated effects and meanings of a person-centred and thriving promoting intervention for nursing home care on resident, relatives’ and staff endpoints. This protocol aims to fill this gap in knowledge [35].

### Theoretical framework

The theoretical framework for the intervention is based on the concepts of *person-centredness*/*person-centred care, thriving* and *caring environments.*

#### Person-centredness/person-centred care

Person-centredness is described as an ethical approach to human interaction, grounded in a fundamental understanding of humans as autonomous reflective persons with capacity and freedom to be the person that they want to be [36]. Implying recognition, respect and trust, person-centredness honours the absolute freedom, value and decision making capacity of each person, regardless of age and physical and cognitive functioning, and emphasises that personhood and dignity needs protection in severe frailty [16]. The ethics of person-centredness is increasingly being operationalised into person-centred care in clinical settings by taking the perspective of the person in need of care as well as the family members as constant point of reference, facilitating shared decision-making, personal authority and choice [15, 16, 37, 38]. In relation to care staff, person-centredredness involves valuing them as individuals by recognising and allowing for the person behind the role to emerge and to draw upon the unique contribution their personalities, experiences, skills and histories can bring to the work [39]. Some models exists that conceptualises the concept of person-centred care, for example Dementia Care Mapping (DCM), the VIPS framework [24, 25], and the Person-Centred Nursing framework (PCN) [40]. These models conceptualises person-centred care as working actively with the older person’s lifestory, personalising care and environment, establishing partnerships and shared decision-making, and prioritising social relations and interactions through the involvement of relatives in the care process.

#### Thriving

Thriving refers to a person’s well-being in relation to the place of stay, and can be understood as a result of an effective mobilisation of both individual and social resources [41], with the aim to support older people’s possibilities to adjust well into their current life situation and the place of stay [42]. As described by Bergland & Kirkevold [42], thriving involves two core and five additional dimensions. The core dimensions represent resident attitudes towards living in a nursing home, and the quality of care and caregivers. The additional dimensions involve qualities in the physical environment, positive relationships with other residents, participation in meaningful activities, opportunities to go outdoors, and relationships with family [42]. Thus, experiences of thriving seem to depend upon how people perceive their present situation in relation to different physical and psychosocial environment factors, i.e. the person-environment interaction and fit [13, 42].

#### Caring environment

The concept of caring environment refers to experiences of an institutions physical and psychosocial environment and the extent to which this is perceived to be caring. Caring environments have been described as emerging from an interaction between aesthetic features of the physical environment and the qualities of people’s doing and being in the environment, influenced by an explicit or implicit philosophy of care [14]. Caring environments have been recognised as influencing satisfaction and wellbeing for nursing home residents, relatives and staff [14], and there is an abundance of previous research showing that the physical environment of care can facilitate or obstruct independence, positive interactions, and meaningful participation in activities [15, 22, 43, 44]. Environments containing objects and symbols that are aesthetically appealing and familiar has also been shown to facilitate positive distractions, and contribute to perceptions of high quality care and wellbeing [14]. Moreover, an aesthetically pleasing environment can be perceived as a way of valuing the life, work and visits of people within nursing home settings [14]. An essential aspect of care staff’s contribution to the caring environment is a willingness to serve in their doing and being, and to do something more than the obvious and expected for residents and their relatives to support positive experiences [14]. Expressions of a willingness to serve have been connected to increased satisfaction with care for residents and relatives [14, 45, 46].

## Methods

The overall aim of the U-Age nursing home study is to evaluate effects and meanings of a person-centred and thriving-promoting intervention in nursing homes. More specifically, the following research questions will be explored:Will the intervention increase resident’s thriving (primary endpoint), and positively affect their experience of the care environment (secondary endpoint)?Will the intervention increase relatives’ satisfaction with care (primary endpoint), enhance their experience of visiting their relative and the nursing home, and positively affect their experience of the care environment (secondary endpoints)?Will the intervention increase staff’s job satisfaction (primary endpoint), decrease their stress of conscience, increase the perceived level of person-centredness of care and positively affect their experience of the care environment (secondary endpoints)?What are the experiences and meanings of the intervention as described by relatives and staff?

The study is designed as a multi-centre, non-equivalent controlled group before-after study with participating sites in Victoria (Australia), Oslo (Norway) and Västerbotten (Sweden). Two nursing homes at each site have been allocated to either intervention or control, in total three intervention and three control facilities across the three international sites. Study specific surveys will be used to collect data on primary and secondary endpoints, with study endpoints being analysed post-intervention, and at six-month follow-up. Qualitative research interviews will be conducted post-intervention to illuminate experiences and meanings of the intervention as described by relatives and staff.

### The intervention

The intervention will be conducted over 12 months and consists of monthly one-hour workshops and reflective evaluation activities between workshops. Inspired by the process and evidence from a previous complex nursing home intervention [35] this intervention will be based on an interactive step-wise pedagogical framework consisting of a) knowledge translation, b) knowledge generation, and c) knowledge dissemination (Table 1).

**Table 1 Tab1:** Overview of the theoretical and pedagogical framework, key dimensions and activities of the intervention

Theoretical framework	Key intervention dimensions
*Person-centredness/person-centred care* *Caring environment* *Thriving*	1. Doing a little extra 2. Developing a caring physical environment 3. Assessing and meeting highly prioritised psychosocial needs
Pedagogical framework	Key intervention activities
*Knowledge translation*	1. One introductory two-hour lecture on the intervention theory and pedagogy for all direct care staff at the three intervention sites.
*Knowledge generation*	2. Monthly reflective, interactive workshops focusing on attaining, analysing, reflecting and discussing evidence in relation to practice. Staff will conduct evaluation tasks between workshops to critically analyse their current routines, environment and care provision in relation to the three intervention dimensions.
*Knowledge dissemination*	3. Staff will report and discuss the knowledge gained from their evaluation task at local site-specific workshops. Staff will also report and discuss the knowledge gained from the intervention at two international knowledge-sharing seminars, one midterm and end-term.

#### Knowledge translation

During the first step, one introductory two-hour lecture will be provided to all direct care staff at the three intervention sites. The aim of the lecture will be to introduce the theoretical framework, pedagogical framework and research-based evidence that underpins the intervention.

#### Knowledge generation

Staff will take part in 12 reflective learning workshops. These workshops will move systematically through the phases of: a) presenting and discussing the best available evidence, b) discussing how research evidence can be understood and implemented in daily care c) identifying and planning for site-based reflection and evaluation activities, c) performing the site-based reflection and evaluation activities, d) participating in follow-up discussions, analyses and reflection on all evaluation activities. The workshops will be led, supervised and supported by university staff from the research group (KS, QL, ÅB), who will guide staff through the processes of attaining, analysing, reflecting and discussing evidence and evaluation activities. The evaluation activities will be conducted between workshops, which means that staff will be asked to critically analyse their current practice, routines, environment and care provision in relation to the three intervention dimensions; doing a little extra, developing a caring physical environment, and assessing and meeting each resident’s highly prioritised psychosocial needs. They will then be asked to report back their experiences at the subsequent workshop.

#### Intervention dimensions

*Doing a little extra.* Participating staff members will be introduced to evidence and understandings on how to facilitate thriving and wellbeing by embodying a willingness to serve in their everyday doing and being, striving to enhance the experiences for residents, relatives and staff by doing a little extra for others. This can mean bringing an unexpected cup of coffee, taking someone outdoors or reporting the latest results from local sports events. Staff will be asked to reflect over and document the little things that they do in everyday activities, actions and interactions with the aim to do something extra for residents, relatives and colleagues to facilitate positive experiences. Documented actions and interactions will be shared and reflected on in the workshops.
*Developing a caring physical environment.* Participating staff members will be introduced to evidence and understandings on how to create an aesthetically appealing physical environment that symbolises quality care and respect for each person’s value and worth. Staff will be introduced to, and discuss, ways in which the physical environment can facilitate positive distractions and community, and facilitate a sense of home and value among residents and relatives. They will also discuss how the physical environment can support relatives’ feeling of being welcomed to the nursing home, as well as expressing and symbolising the value of, and the professionalism expected from, each staff member. Staff will be asked to conduct observations of the physical environment and to interview residents and relatives to explore how the environment of their unit can be improved in order to be experienced as caring. Environmental enrichments in the nursing homes’ common areas, such as shared living rooms, sitting/dining rooms and corridors, will be financially supported by the research group.
*Assessing and meeting highly prioritised psychosocial needs.* Participating staff members will be introduced to evidence and understandings on how to assess, acknowledge and meet each resident’s most highly prioritised psychosocial needs. The residents’ life histories will be used as a tool to facilitate the understanding of each person’s needs and how these needs are prioritised by the residents, together with if and how such priorities change. Staff will be asked to interview residents and relatives with a focus on preferences, values and highly prioritised psychosocial needs. Staff will also participate in group discussions and reflections on how to integrate these needs into the everyday care and routines of the unit, and to decide on the implementation of activities to meet those needs. All staff will be asked to document the activities they conducted to meet the most highly prioritised needs of a resident.

#### Knowledge dissemination

The third step consists of reporting back on the evaluation activities within and across the international sites to facilitate knowledge dissemination between participants. These activities will include two site-specific workshop discussions, as well as mid- and end-intervention international knowledge-sharing. All participating staff members will be invited to report the experiences and results of their reflective evaluation activities to their site-specific colleagues, with a focus on sharing knowledge within units and presenting their experiences, reflections and conclusions. Second, across-site knowledge sharing will be employed where each site will present their processes and achievements through webcasts and recorded presentations.

### Control facilities

The staff at the three control facilities will receive the same introductory two-hour lecture on the theoretical and practical foundations of person-centredness, person-centred care, thriving and caring environment as the intervention sites. Following this lecture, they will continue their practice without further involvement from the research team. Once the research project has been completed, the control facility will be provided the intervention protocol and support to facilitate implementation of the intervention.

### Inclusion criteria, recruitment, and study sample

To be included in the study, nursing homes must meet the following inclusion criteria: a) managers expressing a need and willingness to participate and support the intervention, b) having about 50 resident beds, and c) employing at least 50 staff members. The recruitment of eligible nursing homes will be purposively conducted at each international site using the researchers’ clinical networks. Nursing home managers will be given/provided verbal and written information on the eligibility criteria, the purpose of the study, the intervention and its implementation process. Before commencing the study, written information and a formal invitation to participate in the data collection will be given to all staff members at the nursing homes where managers have consented to participate.

Participants will be included continuously during the intervention, with the following inclusion criteria: residents need to have lived in the nursing home for >1 month by the time of data collection; relatives need to visit the nursing home on a regular basis (>1/month); staff need to work in the nursing home on a temporary and or permanent basis (>1 month contract), and have been working >1 month in the nursing home by the time of data collection. The goal will be to include at least 900 participants in the study; 300 residents, 300 relatives, and 300 staff members. All eligible persons will be given written information on the purpose and outline of the study, and will be given the opportunity to ask the researchers questions regarding the study throughout the study period.

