## Discussion

This protocol outlines the design and procedure for an international multi-site trial within nursing homes. Factors such as limited research cultures, high turnover of staff and residents, and unpredictable external forces such as regulatory organisational changes, suggest that conducting complex interventions in nursing homes is challenging [60]. Therefore, this study protocol can be regarded an important blueprint for both the conduct and evaluation of the intervention, as well as for the communication of information to stakeholders and/or the scientific community. A number of elements and processes are described based on experiences from interventions carried out in similar contexts, such as the theoretical and pedagogical framework for the intervention [61–64]. Anchoring the intervention in a theoretical framework consisting of established theories and evidence-based interventions, as well as a pedagogical framework that moves between knowledge translation, generation and dissemination is a strength of the study. Additionally, previous experiences from similar implementation protocols [35, 63] can be seen as strengthening the study.

The multisite approach can be a strength as well as a weakness of the study, a strength in the sense that the processes, experiences and results will have international applicability and relevance, and a weakness in the sense that there are dimensions that risks deviating slightly between sites. Thus, balancing contextual relevance with standardised content will be a challenge. To secure that the intervention will be as identical as possible across the three sites, the same detailed education material and facilitators guide will be used across sites, and weekly calibration meetings will be held between the three researchers leading the intervention at each site. The collaboration between the research group and the nursing home management and direct care seems essential for a successful intervention. Therefore, the choice of including nursing homes from the researchers’ existing network is regarded as a strength of the study. However, this also excludes the possibility of other nursing homes in need for improvement to participate. Thus sample representativity can be seen as a weakness of the study.

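### The resident target of 150 per group equals the bed capacity of three homes, with no allowance for non-response, so the resident sample behind the stated 0.85 power is not plausibly available at any one wave

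*Protocol article*

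**What the plan says.** The Methods section describes "in total three intervention and three control facilities across the three international sites". Under Inclusion criteria, recruitment, and study sample, an eligible home is defined by "having about 50 resident beds, and c) employing at least 50 staff members", and the goal reads "The goal will be to include at least 900 participants in the study; 300 residents, 300 relatives, and 300 staff members". The same section adds "Participants will be included continuously during the intervention" and "residents need to have lived in the nursing home for >1 month by the time of data collection".

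The Power calculation section uses effect size 0.30, two-sided 0.05 and power 0.85. For TOPAS (mean 154, SD 22) it concludes that 150 residents per group can detect a pre-post difference of 6.2. It repeats 150 per group for relatives and for staff and arrives at 900 in total.

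Data collection is by anonymous survey at three waves: baseline, after the 12-month intervention, and six months later. The Discussion names "high turnover of staff and residents" as a known difficulty of research in this setting.

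**The concern.** The number of residents required in each group is the same as the number of beds in each group. A survey wave would have to find every bed occupied by someone who has stayed more than a month, consents and responds. The sample size contains no margin for anything less, and the article itself warns of turnover.

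The article does not say what the 150 counts. It could be distinct residents ever included, respondents at each wave, or residents measured both before and after. Only the first can be reached with ordinary participation, and it is not the count that determines the precision of a pre-post difference. If late entrants were added to the tally, the trial could report its target as met while fewer than 150 per group had answered at every wave. Residents' thriving is a primary endpoint, so its stated power should describe a sample the homes can supply.

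**Working it through.** **Inputs.** Three homes per group (Methods); about 50 beds per home and a target of 300 residents (Inclusion criteria, recruitment, and study sample); SD 22, difference 6.2, effect size 0.30, two-sided 0.05, power 0.85 and n = 150 per group (Power calculation). The article gives no participation or turnover rate, so those below are assumptions.

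**1. Capacity.** 3 x 50 = 150 beds per group and 6 x 50 = 300 in all. The target is 150 and 300. The total of 900 is 3 populations x 2 groups x 150, so no inflation for loss is included.

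**2. The plan's own figure.** Two-sample comparison, n per group = 2 x (1.960 + 1.036)² / d².
- For d = 6.2 / 22 = 0.282, n = 227.
- For d = 0.30, n = 200.

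Neither gives 150. With n = 150 the power is 0.74 at d = 0.30 and 0.68 for 6.2, and the difference detectable with 85% power is 7.6. This shortfall exists even with every bed filled and responding, so it is not due to capacity. The effect of capacity must therefore be measured from 7.6, not from 6.2.

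**3. Per-wave numbers at less than full participation.** n = 150 x participation; two-sample t-test, SD 22, before clustering.

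| Participation (assumed) | n per group | Power, d = 0.30 | Power, 6.2 | Detectable at 85% |
|---|---|---|---|---|
| 100% | 150 | 0.74 | 0.68 | 7.6 |
| 80% | 120 | 0.64 | 0.58 | 8.5 |
| 60% | 90 | 0.52 | 0.47 | 9.9 |

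The normal approximation gives 0.59 instead of 0.58, and 9.8 instead of 9.9; the other entries agree to the digits shown. To obtain 150 respondents per group at these rates, each home would need 50 / 0.80 = 62.5 or 50 / 0.60 = 83 beds.

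The detectable difference scales with 1/√n. It therefore grows by √(150/120) = 1.12 or √(150/90) = 1.29 under any similar formula, whatever pre-post correlation is assumed.

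**4. What continuous inclusion changes.** An illustrative cumulative count is 300 x (1 + yearly turnover x years) x response. With 80% response it runs from 300 x (1 + 0.20 x 1) x 0.80 = 288 to 300 x (1 + 0.40 x 1.5) x 0.80 = 384. A cumulative 300 is therefore reachable. But a resident admitted after baseline adds nothing to the baseline count, and at a later wave takes a bed that someone else has left. The per-wave ceiling stays at about 150 per group.

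**5. Only if the 150 are the same residents measured twice.** With an assumed further loss of 20% to 40%, n runs from 120 x 0.80 = 96 to 90 x 0.60 = 54 per group. On the same two-sample basis the detectable difference is 9.6 to 12.8.

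**The case against.** The strongest reply is that the article plans continuous inclusion and appears to test eligibility at each data collection. That, together with anonymous surveys, fits an open cohort or repeated cross-sections at least as well as a closed cohort. Later entrants then inform the post-intervention mean, and the planned mixed models can use people seen at only one wave. This stands. It removes retention from the argument unless the 150 is meant as a paired number. It does not raise the count at any wave above the number of beds.

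A reader might infer more than the article supports:
- **That every resident must respond and stay, or that the target cannot be delivered.** Replacement residents can bring the cumulative count to 300, and the bed figure is approximate.
- **That late entrants are useless for the pre-post comparison.** The mixed model can use them. They simply do not fill a per-wave or paired requirement.
- **That relatives and staff face the same ceiling.** The criterion for staff, "employing at least 50 staff members", is a floor. Nothing limits participation to one relative per resident, and the stated difference of 8.7 with SD 21 needs only about 105 relatives per group by the two-sample formula.
- **That the whole gap from 6.2 is due to participation.** Step 2 of the working shows that part of it is present at a full 150.

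It is also fair to say that detailed attrition assumptions may sit in the full protocol. However, the published target and the published bed numbers already coincide, and the published total contains no margin.

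**Conclusion.** The point holds for residents. About 150 per group is the most that three homes of about 50 beds can supply at baseline or at any later wave, and the power statement uses all of it. On a two-sample basis before clustering, participation of 80% to 60% lowers power at effect size 0.30 from 0.74 to between 0.64 and 0.52. It raises the detectable TOPAS difference from 7.6 to between 8.5 and 9.9. The larger figures of 9.6 to 12.8 apply only if the 150 means residents measured both before and after, which the article does not say.

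The capacity arithmetic comes from the article. The sizes rest on assumed participation and loss rates and on a two-sample comparison with SD 22. The article states neither a rate, nor a pre-post correlation, nor the exact test behind its calculation.

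**What to change.** 1. State that about 150 residents per group per wave is the ceiling set by the homes.
2. Say whether the 150 is cumulative, per wave or paired.
3. Restate resident power and detectable difference for the expected number of respondents per wave, over a stated participation range. If individuals are linked across waves, do the same for those with both surveys.
4. Keep late entrants in the mixed model, but do not count them cumulatively as meeting a per-wave or paired number. Report the number per wave, and the paired number if it exists, beside the cumulative total.

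The cost is some wording and one recalculation. No further recruitment is required. The downside is that the stated resident power will look less favourable.
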